**Abstract**

Approximately 1 million children < 5 y living in sub-Saharan Africa die from severe anemia annually. This severe anemia frequently results from coexisting iron deficiency and malaria infection, but the standard of care, concurrent iron therapy and antimalarial treatment, has proven ineffective at curing the profound anemia and has promoted proliferation of the parasite in some studies. The pro-inflammatory immune response mounted against malaria down-regulates iron absorption in the gut, making provision of oral iron supplements during malarial infection of questionable utility. The present study uses iron stable isotopes and a randomized design to test whether starting 4 weeks of iron therapy immediately after antimalarial treatment or 4 weeks later is associated with greater iron incorporation into red blood cells at the time of initial administration of iron therapy and improved long-term hematological recovery. One hundred Ugandan children 6-59 mos with anemia (hemoglobin 5-9.9 g/dL) and with clinical signs of malaria who present to the Pediatric Acute Care Ward of Mulago Hospital in Kampala, Uganda, will be randomized to start iron immediately after antimalarial treatment on Day 0 (immediate group) or 4 weeks later on Day 28 (delayed group). Children will be assessed at the hospital on Day 0, Day 28 and Day 56 and will receive bi-weekly home visits for the 56-day study duration. The specific aims and corresponding hypotheses of the proposed study are:

**Aim 1: Identify the sequencing of antimalarial treatment and iron therapy that results in the greatest red cell iron incorporation at the time of initial iron supplement administration.** The working hypothesis is that red cell iron incorporation will be greater at the time of initial supplement administration in children starting iron 4 weeks after antimalarial treatment (delayed group) compared to children starting iron concurrently with antimalarial treatment (immediate group), due to more complete parasite clearance and resolution of inflammation, permitting better iron uptake, distribution, and utilization.

**Aim 2: Determine whether long-term hematological recovery is impacted by immediate vs. delayed iron.** The working hypothesis is that delayed iron treatment will be associated with greater hemoglobin and improved iron status at Day 56 compared to immediate treatment due to more complete parasite clearance and consequent improved iron absorption and use in the delayed group.

The results of this study will establish a physiologically-based framework for the optimal timing of antimalarial treatment and iron therapy upon which future interventions aimed at improving iron status in malaria-endemic regions can be built, thus helping to reduce the morbidity and mortality and ensure the full neurobehavioral development of the millions of severely anemic children suffering from iron-deficiency and malaria.

**Protocol Overview**

| Title | Acute vs. delayed iron: effect on red cell iron incorporation in severe malaria |
| --- | --- |
| Description | Prospective study of the effect of immediate vs. 4-week delayed oral iron therapy on red blood cell iron incorporation and long-term hematological recovery in Ugandan children aged 6-59 months with anemia (Hb 5-9.9 g/dL) and signs of clinical malaria (positive malaria blood smear + fever in past 24 hours or tem) who present to the Paediatric Assessment Center or Paediatric Acute Care Unit at Mulago Hospital, Kampala, Uganda. Red blood cell iron incorporation on Day 0 and on Day 28 will be measured directly, using iron stable isotopes. |
| Study aims | Aim 1: Identify the sequencing of antimalarial treatment and iron therapy that results in the greatest red cell iron incorporation at the time of initial supplement administration (Day 0 incorporation immediate group vs. Day 28 incorporation delayed group).  Aim 2: Determine whether long-term hematological recovery is impacted by immediate vs. delayed iron (Change in hemoglobin and other iron markers between Day 0 and Day 56). |
| Clinical sites | Mulago Hospital, Kampala, Uganda. |
| Laboratory sites | **Infectious Diseases Institute Core Lab (Mulago Hospital):** Routine onsite testing, including assessment of complete blood counts and preparation of thick and thin smears for malaria parasites. Core lab personnel will also centrifuge blood samples and aliquot plasma to be sent to the U. S. for analysis of iron and inflammatory indicators and will prepare red blood cell pellets for shipment to the U.S. for isotopic analysis.  **[name] research laboratory in McGuire Translational Research Facility at the University of Minnesota:** Assessment of iron indicators [ferritin, transferrin receptor (TfR), hepcidin] and inflammatory markers C-reactive protein (CRP) and alpha-1-glycoprotein (AGP) in plasma with immunoassay.  **Laboratory of [name], Baylor College of Medicine:** calculation of isotope enrichment fractions in red blood cells using inductively coupled mass spectrometry (ICP-MS). |
| Study participants | Consecutive sample of 100 anemic (Hb 5.0 – 9.9 g/dL) Ugandan children aged 6-59 mo with clinical malaria (positive blood smear and fever in past 24 hours). |
| Selection criteria | Inclusion criteria:   1. 6 - 59 months of age 2. Hemoglobin 5.0 - 9.9 g/dL according to HemoCue 3. Fever in past 24 hours or temperature ≥37.5 4. *P. falciparum* on blood smear at Acute Care Unit 5. Residence <50 km of study hospital   Exclusion criteria:   1. Impaired consciousness on physical exam 2. Seizure activity prior to or during admission 3. Acute malnutrition 4. Known sickle cell disease |
| Study design and procedure | **Day 0**: A venous blood sample is routinely taken from children who present in Acute Care with clinical malaria and anemia (hemoglobin <10 g/dL). Once informed consent is obtained from the caregiver, drops of whole blood will be used to assess erythrocyte protoporphyrin (EP). The EP result will be known immediately. If the child is iron-deficient (EP ≥ 80 µmol/molheme), he or she will be randomized to receive iron before discharge from the hospital (immediate group) or 4 weeks later (delayed group). Iron and inflammatory markers (ferritin, sTfR, hepcidin, reticulocytes, CRP, AGP) will be assessed in each child’s baseline blood sample.  Once consent is obtained and the child is enrolled in the study, each child will be given an oral dose of stable, non-radioactive iron isotope 57Fe mixed with fruit juice,(mango or orange) following a two-hour fast. Caregivers of children in the immediate group will be instructed how to properly administer the first dose of oral iron therapy to be given the following day (Day 1). Iron therapy will consist of a 4-week course of daily ferrous sulfate syrup, based on 2 mg iron/kg body weight.  **Day 28 follow-up visit**: All study children will return to the hospital. A finger prick blood sample will be taken for hemoglobin assessment and for preparation of a Giemsa smear. A venous blood sample will be drawn from all children and sent to Core Lab. Plasma will be collected for assessment of iron and inflammatory markers, and red blood cells will be collected and sent for isotopic analysis. After a two-hour supervised fast, all children will then receive an oral dose of stable, non-radioactive iron isotope 58Fe in an identical manner as on Day 0. Caregivers of children in the delayed iron group will be instructed how to administer the first daily dose of iron syrup to be given the following day (Day 29).  **Day 56 follow-up visit**: On Day 56 all children will return to the hospital for a final finger-prick blood sample (Hb and Giemsa) and venous blood draw (plasma markers plus isotopic analysis) and assessment.  Home monitors will conduct bi-weekly home visits of each child during the 56-day study period to ensure supplement compliance and to assess and record any side effects. Any ill child will be referred to Mulago Hospital and will be provided transportation free of charge. |
| Outcomes | Aim 1: Primary outcome: Percentage of red cell iron incorporation at the time of initial iron supplement administration (Day 0 incorporation immediate group vs. Day 28 incorporation delayed group)  Secondary outcomes: Association between change in plasma iron and inflammatory indicators (EP, ferritin, sTFR, hepcidin, reticulocytes, CRP, AGP; all continuous) and change in percentage red cell iron incorporation in each treatment group between Day 0 and Day 28.  Aim 2: Primary outcomes: Change in hemoglobin from Day 0 to Day 56 in immediate vs. delayed groups.  **Secondary outcomes:** Change in iron markers (EP, ferritin, sTFR, hepcidin) from Day 0 to Day 56 in immediate vs. delayed groups. |

**Significance**

Approximately 25% of the world’s population is anemic.^1^ Globally, iron deficiency and malaria are primary contributors to this anemia, and where the conditions coexist, the resulting anemia is often severe and disproportionately affects young children. The rapid growth of children < 36 months, combined with diets low in bioavailable iron and high in compounds that inhibit iron absorption, make these children vulnerable to dietary iron deficiency, while naïve immune systems with little acquired immunity permit malaria to have particularly harmful health effects. Administering iron in malaria-endemic areas, however, may be dangerous, as excess iron can enhance the growth and pathogenicity of microorganisms.^2^ The established neurobehavioral consequences of untreated iron deficiency, however, necessitate development of effective and safe strategies to provide iron in areas where malaria and other infections are prevalent. Recent research, italicized below, suggests that identification of the sequencing of iron and antimalarial therapy that optimizes iron status and reduces morbidity risk may lay the foundation of any successful strategy

- The *current recommendation for combined treatments for malaria and iron deficiency is not working.* Despite the World Health Organization’s current recommendation that infants and children who have malaria and are diagnosed with iron deficiency or severe anemia “be treated with antimalarial and, where appropriate, antibiotic therapy as well as iron therapy,”^3^ evidence of the effect of combined iron and antimalarial treatment on hemoglobin concentration in young children in malaria-endemic areas has been mixed, and reports of increased malaria parasitemia and clinical episodes are frequent.^4-6^
- *Paradigm shift: Clearing malaria and associated inflammation first and then providing iron may enhance the efficacy and reduce the risk of both interventions*. Strong evidence of hepcidin concentrations^7^ and red blood cell iron incorporation in *P.-falciparum*-infected children^8^ supports the hypothesis that both antimalarial treatment and iron therapy would be most efficacious if not administered concurrently and that a delay of approximately four weeks after antimalarial treatment would ensure reduction of inflammation and optimal incorporation of oral iron.
- If our hypotheses that delaying iron until 4 weeks after antimalarial treatment optimizes red blood cell iron incorporation and improves long-term hematological recovery proves to be correct, malaria and iron deficiency intervention programs adopting this sequencing strategy could both reduce the immediate morbidity and mortality as well as ensure the full neurobehavioral development of the millions of iron-deficient children who live in malaria-endemic regions.

**INNOVATION**

- By employing direct methods to track oral iron and its incorporation into red blood cells in children receiving iron concurrently with antimalarial therapy or four weeks later, the proposed study will establish the sequencing of these interventions that optimizes their efficacy, providing a physiologically-based framework for future malaria and iron deficiency treatment programs.
- This 4-week delay has not been tested directly using both stable iron isotopes and a randomized design, nor has it been investigated in children with severe anemia and clinical malaria, in whom the mortality burden is great.

**Background**

As in many regions of the world, including sub-Saharan Africa, Southeast Asia, and Central and South America, where iron deficiency and malaria coexist, the prevalence of anemia among children younger than three years living in Uganda is an estimated 66-77%.^9^ The results of a recent large, randomized, placebo-controlled trial on Pemba Island, Tanzania^10^ underscored the potential danger of providing iron in malaria-endemic regions to address this prevalent anemia, finding that children who received iron supplements were more likely to experience a serious adverse event, i.e., death or hospitalization, than children who received placebo. Although a sub-study of the trial indicated that the harmful effect of iron was limited to children who were iron-replete at baseline, the question of how to treat both conditions safely and efficaciously in malaria-endemic areas remains largely unanswered. Although several studies report modest (~ 1g/dL) gains in hemoglobin concentration among children receiving concurrent iron and antimalarial therapy in accordance with WHO guidelines,^4-6,11^ this gain is typically not sufficient to cure the profound anemia of the majority of children. Further, many authors report non-statistically significant increases in malaria indices among children receiving iron, including increased parasitemia^4, 5^and increased risk of malaria attack.^6^Noting that a larger proportion of the iron-treated patients failed to clear their parasitemia, Nwanyanwu et al. concluded that antimalarial treatment should be given first, followed by iron therapy, if needed.^5^

The pathophysiology of anemia resulting from co-existing iron deficiency and malaria infection supports this conclusion.The anemia of malaria is complex, with hemolysis of parasitized red blood cells, clearance of both parasitized and non-parasitized red blood cells by reticulo-endothelial macrophages, and impaired bone marrow activity all contributing.^12,13^ Iron that would normally be recycled from degraded red blood cells and transported to the bone marrow for erythropoiesis is instead sequestered in reticulo-endothelial stores under the influence pro-inflammatory cytokines IL-1, IL-6, TNF-α, IFN-γ, the same cytokines implicated in contributing to the alterations in iron metabolism characteristic of the anemia of chronic disease.^14-17^ The antimicrobial hepatic protein hepcidin, an integral regulator of iron metabolism that serves as the soluble messenger among the sites of iron absorption, erythropoiesis, and storage,^18^also plays a key role in these inflammatory changes. Hepcidin concentrations rise during iron sufficiency, down-regulating intestinal iron absorption, and fall during iron deficiency, up-regulating iron absorption. Hepcidin is also a positive acute phase response protein whose concentrations are up-regulated during inflammation under the influence of IL-6^19^--a finding that is thought to explain the alterations of iron metabolism (hypoferremia, hyperferritinemia, anemia) during infectious and non-infectious inflammatory states. Hepcidin acts primarily by binding and degrading the iron-exporting protein ferroportin,^20,21^ blocking iron efflux from intestinal and reticulo-endothelial cells. Multiple studies have confirmed that hepcidin concentrations increase with *P. falciparum* infection^7, 22,23^ and that even mild increases in serum hepcidin can lead to profound disturbances in iron metabolism, including marked hypoferremia, increased serum ferritin, and reduced incorporation of hemoglobin into reticulocytes.^7^

These changes appear to be resolved approximately four weeks after successful antimalarial treatment. One recent study of *P. falciparum*-infected, hospitalized Tanzanian children aged 2 mo-13 y who were anemic and febrile found that urinary concentrations of hepcidin at baseline were high and were associated with hypoferremia and increased serum ferritin.^7^ Antimalarial treatment rapidly decreased hepcidin concentrations and reversed hypoferremia. Serum iron concentrations and transferrin saturation rose rapidly, but significant changes in total iron binding capacity and serum ferritin were observed only after four weeks. Concentrations of CRP and pro-inflammatory cytokines IL-1Ra and IL-6 paralleled the changes in hepcidin, falling significantly two days after antimalarial treatment and declining even further by Week 4. The authors concluded that marrow suppression in patients with febrile malaria is rapidly reversible with efficacious antimalarial treatment and that iron therapy might only be effective once hepcidin concentrations decline. A study of red cell iron incorporation in young Gambian children treated for uncomplicated malaria and given a 30-day course of iron similarly demonstrated that iron therapy might be most efficacious if given 2-4 weeks after antimalarial treatment.^8^Using iron stable isotopes, researchers found that children recovering from malarial anemia exhibited significantly lower red cell iron incorporation at baseline and at Day 15 (baseline: 8% vs. 28%, p<0.001; Day 1: 14% vs. 26%, p=0.04), but had a greater hemoglobin concentration on Day 15 and Day 30 than children with iron deficiency anemia alone, leading researchers to conclude that children in the post-malaria group met their immediate iron needs for erythropoiesis with recycled iron liberated from reticulo-endothelial stores after antimalarial treatment rather than from the oral supplement. Whether this hemoglobin recovery would have been even greater if the iron therapy had been delayed until red cell iron incorporation was more optimal, i.e., some time after Day 15, is unknown. Also unknown is whether iron absorption and subsequent incorporation into red cells would follow similar patterns in children with severe anemia and clinical malaria in whom inflammation-induced iron trapping and subsequent hypoferremia is likely more profound. To date, red cell iron incorporation during malaria infection has only been investigated in two populations, Gambian children with uncomplicated malaria, as described, and young Beninese women of childbearing-age with subclinical malaria.^24^

**Study Procedure**

**Overview:** We will recruit Ugandan children aged 6-59 months with anemia (hemoglobin 5 – 9.9 g/dL) and with clinical evidence of malaria who present to the Paediatric Assessment Center and the Paediatric Acute Care Unit at Mulago Hospital in malaria-endemic Kampala, Uganda. All children will be treated for malaria, and any child found to be iron-deficient [erythrocyte protoporphyrin (EP) ≥ 80μmol/mol heme] will be randomized to start a 4-week course of daily iron therapy (2 mg/kg) immediately on Day 0 (immediate group) or 4 weeks later on Day 28 (delayed group). All children will return to the hospital on Day 56 for final assessment (**Figure 1**). To determine the percentage of oral iron incorporated into red blood cells on Day 0 and Day 28, all children will be given an oral dose of iron stable isotope, 57Fe, on Day 0 and an oral dose of a different iron stable isotope, 58Fe, on Day 28. Calculation of isotopic enrichment of the red blood cells 28 days after dosing will permit comparison of red blood cell iron incorporation at the time of initial administration of the iron supplement between the treatment groups (Day 0 incorporation for immediate group vs. Day 28 incorporation for delayed group, Aim 1). Comparison of the change in hemoglobin and other iron markers (erythrocyte protoporphyrin, ferritin, soluble transferrin receptor, hepcidin, reticulocytes) from Day 0 to Day 56 between treatment groups will enable assessment of how immediate vs. delayed iron impacts long-term hematological recovery and iron status (Aim 2).

Study Recruitment and Enrollment: We will recruit a consecutive sample of 100 children with Hb 5.0-9.9 g/dL and between the ages of 6-59 months who present to the Pediatric Acute Care unit at Mulago Hospital, Kampala, Uganda. The inclusion and exclusion criteria are as follows:

Inclusion criteria:

1.) 6 - 59 months of age

2.) Hemoglobin 5.0 - 9.9 g/dL according to HemoCue

3.) Fever in past 24 hours or temperature > 37.5

1. *P. falciparum* on blood smear at Acute Care Unit
2. Residence < 50 km of study hospital

Exclusion criteria:

1. Impaired consciousness on physical exam
2. Seizure activity prior to or during admission
3. Acute malnutrition
4. Known sickle cell disease

**Day 0 Procedure:** Children younger than 5 years who present to the Paediatric Assessment Center or Paediatric Acute Care Unit with a positive blood smear will have a finger-prick blood sample for hemoglobin and preparation of Giemsa smear as part of routine care. If hemoglobin is 5.0 – 9.9 g/dL, the Giemsa smear is positive, and the child lives < 50 km from the hospital, the child will be eligible for the study. After informed consent for our research study is obtained (see Informed Consent, below), a venous blood sample will be drawn. Blood samples are routinely drawn on children with this clinical presentation as part of standard of care. After informed consent for our research study is obtained (see Informed Consent, below), drops of whole blood will be dispensed for immediate determination of EP by hematofluorometer (Aviv Biomedical, Lakewood, NJ) and for preparation of a reticulocyte smear. The remaining blood will be sent to Corelab for collection of plasma. Children found to be iron-deficient (EP ≥ 80 µmol/molheme) will be randomized to start 4 weeks of daily iron therapy at baseline, once oral medication can be tolerated (immediate group), or 4 weeks later on Day 28 (delayed group). Any child who is not iron-deficient will not receive iron therapy. Upon enrollment all children will be assigned a randomly generated, unique study identification number that will link clinical forms and samples. Caregivers will be given a clinical follow-up schedule, with dates of bi-weekly home visits and Day 28 and Day 56 hospital visits indicated. On Day 0, participants will be given 2500 USh for transport home. On both the Day 28 and Day 56 visits, participants will receive reimbursement commensurate in value to 15,000 USh. 5000 USh will be given to cover transportation costs to and from the hospital and any cell phone air time needed in the preceding 4 weeks to report illness, and a food package containing oil, rice, and/or sugar valuing 10,000 USh.

**Informed consent:** Once each eligible child is medically stable, a study representative will conduct the informed consent process. The iron study consent form describing the study, including risks and benefits of study participation, will be presented in either Luganda or English, depending on the parent’s preference. Translators will be available if needed. Study staff will explain that not participating in the study or deciding to stop participation will not jeopardize the child’s care. Copies of signed consent forms will be kept on file at the study research offices at Mulago Hospital.

**Randomization:** A list of 100 random, 3-digit numbers will be computer-generated at the University of Minnesota. These numbers will serve as unique study identification numbers. Treatment group (either immediate or delayed) will be then be randomly assigned to each number, in blocks of four. The treatment group for a particular study ID will be placed in a sealed envelope. Envelopes will be opened sequentially by study personnel at patient enrollment.

**Clinical treatment:** Clinical treatment of all children who are enrolled in the study will be overseen by [name]. Ugandan national guidelines will be followed for treatment of malaria, presently oral quinine for hospitalized patients and artemethar combination drugs for outpatients. Initial labs and testing will be done by study physicians and nurses, but clinical care of all patients will be given by the house staff and attending physicians of Mulago Hospital. Other co-infections and medical problems will be treated according to standard protocols of Mulago Hospital. Thick and thin blood smears will be prepared for all enrolled children to look for malaria parasites and density of parasitemia, calculated using parasites per 200 WBC.

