**Sample size calculations:** Based on variation between children in 57Fe incorporation reported in Doherty et al.,^8^40 children are needed in each group to provide a clinically significant, detectable difference in red cell incorporation between groups of 4.5%, assuming 80% power and alpha=0.05 (**Table 1**). To account for 20% loss to follow-up, we will recruit 50 children in each group.

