**Collaborating sites:** This study will take place at Mulago Hospital in Kampala, Uganda. Mulago is the largest referral hospital in Uganda, and our group has collaborated with pediatric malaria researchers there for more than a decade. For the current study, on-site collaborators will be responsible for patient enrollment and care while in the hospital, administration of study interventions, obtaining and proper care of study samples, and coordination of follow-up for the duration of the study period. Our on-site data team will ensure complete data entry from clinical forms, collected in the hospital and in the field, and will conduct periodic quality checks on data integrity and completeness. All study forms will be kept in a locked desk in the Cerebral Malaria Team office, and the study database will be password-protected.

**Description of research material obtained**: Blood samples will be collected from all enrolled children at baseline, at Day 28, and at Day 56. From these blood samples, plasma will be collected, frozen, and shipped to the US for analysis of iron markers. The red blood cell pellet from each blood sample will be suspended in saline, frozen, and also shipped to the US for analysis of isotope ratios. Data from clinical forms will be kept in a password-protected database, which is routinely backed up. Paper copies of forms will be kept in a locked office. Any shared data set will be stripped of all patient identifiers.

**Description of data:** We expect to collect data on the concentrations of iron and inflammatory markers in the plasma of all enrolled children at 3 time points. We also expect to gain values of red cell iron incorporation at Day 0 and Day 28. We will further have morbidity data for the 56-day duration of the study, including the number of malaria episodes and fevers.

**Linkages and access to subject identities:** The study coordinator, home visitors, nurses, and data manager will have access to identifiable information, as it is necessary to ensure full follow-up, patient care, and accurate data entry and storage.

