**ADEQUACY OF PROTECTION AGAINST RISKS**

**Plans for recruitment and informed consent:** Study participants will be recruited in the Pediatric Acute Care Unit of Mulago Hospital. Informed consent will be obtained from parents or guardians of all study participants, with information on risks and benefits being provided and consent forms being given to the parents or guardians in the local language. Data will be stored in a locked office accessible only to study personnel. Caregivers of potential participants will be informed that their child can leave the study at any time without jeopardizing the care they will receive at Mulago Hospital. No study-specific tests will be administered before informed consent is obtained.

**Circumstances of consent:**Consent will be sought and obtained from caregivers bringing eligible children into the Pediatric Acute Care Unit. Once the patient is medically stabile, the Medical Officer on duty will approach the caregiver and inform him or her about the study and will provide a full description of risks and benefits of study participation. The consent form will be available in both English and Luganda, the local language. The caregiver will acknowledge consent by signing the form.

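### A constant, published block size of four at a single unmasked site lets staff deduce an expected third of allocations; varying the block size is a cheap improvement

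*Protocol*

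**What the plan says.** The scheme is set out in the Randomization paragraph of Study Procedure. The identification numbers come from off site: "A list of 100 random, 3-digit numbers will be computer-generated at the University of Minnesota". Arms are then attached to them: "Treatment group (either immediate or delayed) will be then be randomly assigned to each number, in blocks of four". No other block size and no stratification factor is mentioned.

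Concealment is by envelope: "The treatment group for a particular study ID will be placed in a sealed envelope". The envelopes are used in order and on site: "Envelopes will be opened sequentially by study personnel at patient enrollment".

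There is one running sequence, since "This study will take place at Mulago Hospital in Kampala, Uganda". The arms are equal in size: "To account for 20% loss to follow-up, we will recruit 50 children in each group".

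Treatment is visible from the first visit. Under Protocol Overview, Day 0, "Caregivers of children in the immediate group will be instructed how to properly administer the first dose of oral iron therapy", while the delayed group gets its syrup instructions on Day 28. No placebo or masking of staff is described.

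Staff contact with the family comes before allocation. Under Circumstances of consent, once the child is judged stable, "the Medical Officer on duty will approach the caregiver and inform him or her about the study". The Day 0 Procedure places the EP test after consent, and only children at or above the EP threshold are randomized.

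**The concern.** A sealed envelope hides an allocation only if it cannot be worked out from earlier ones. Here four conditions for working it out are met together: a constant block size, its publication in the protocol, a single sequence, and past allocations that site staff can see. Toward the end of a block, staff who keep count can tell which arm comes next.

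Some discretion is exercised before the envelope is opened: when a child counts as medically stable, when the caregiver is approached, and how consent is encouraged. If the next arm can be foreseen, any of these could be influenced by it, even unintentionally. Opinions about the arms are plausible: the protocol hypothesizes that delay is better, calls concurrent iron the current standard of care, and names more malaria episodes as the primary risk of iron.

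What is at stake is comparability of the arms at baseline, for example in hemoglobin or inflammation. Both primary analyses are unadjusted two-sample t-tests. The secondary adjustment lists for the two primary outcomes do not name baseline hemoglobin or inflammatory markers, although they are introduced by the word including and so may not be exhaustive.

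**Working it through.** **Inputs from the Protocol.** Block size 4; two arms of 50; one list of 100; one site; no stratification stated. The plan gives no predictability figure to reproduce. Its group size does reproduce: 40/(1 − 0.20) = 50 per group, so 100 children, or 100/4 = 25 blocks of two immediate and two delayed.

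**Certain allocations, constant blocks of four.** A block has 4!/(2!·2!) = 6 equally likely orders. The next allocation is certain when one arm is already used up.

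| Position in block | Probability that it is certain | Probability that the best guess is right |
| --- | --- | --- |
| 1 | 0 | 1/2 |
| 2 | 0 | 2/3 |
| 3 | 2/6 = 1/3 | 1/3 × 1 + 2/3 × 1/2 = 2/3 |
| 4 | 1 | 1 |
| Sum | 4/3 | 17/6 |

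- Share certain: (4/3)/4 = 33.3%.
- Best-guess rate: (17/6)/4 = 17/24 = 70.8%. Under simple randomization it is 50%.
- Over 25 blocks: 25 × 4/3 = 33.3 allocations expected to be certain. Each block contributes 1, or 2 with probability 1/3, so the SD is √(25 × 1/3 × 2/3) = 2.4 and the count cannot fall below 25.

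**Randomly varied blocks.** Lists of 100 were simulated with block sizes drawn at random with equal probability. The observer knows the possible sizes but not their order, and updates after each allocation.

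| Block sizes | Certain | Best guess right |
| --- | --- | --- |
| 4 only | 33.3% | 70.8% |
| 4 and 6 | about 5.5% | about 69% |
| 4, 6 and 8 | about 2.3% | about 68% |

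Varied sizes thus remove most of the certainty but little of the guessing advantage.

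**Cost in balance.** If the list is cut at 100, only the last block can be incomplete, and a block of size b can leave the arms at most b/2 apart: 3 children with sizes 4 and 6, or 4 with sizes 4, 6 and 8. At 52 against 48, the variance of a difference in means rises by the factor (1/52 + 1/48)/(2/50) = 1.0016, which is negligible.

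**Scale of a possible imbalance (assumption, not a protocol figure).** Suppose staff acted on every certain allocation and on no others, so that the third of each arm that is steered had mean baseline hemoglobin higher by s in one arm and lower by s in the other. The expected baseline gap is 2 × s/3. For s from 0.25 to 0.5 g/dL this is 0.17 to 0.33 g/dL. The Aim 2 design difference is 1.10 g/dL, but that is a difference in 56-day change. How much of a baseline gap would carry over to it cannot be derived from the protocol.

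**The case against.** The strongest reply is that permuted blocks in sealed envelopes are conventional and that the protocol already has safeguards. Much of this stands.

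- **Consecutive sample.** It is stated in Protocol Overview, Study Recruitment and Enrollment, and Sampling plan, and it leaves less room to choose among eligible children. Entry also rests largely on measurements or facts: age, HemoCue hemoglobin, smear, residence. It does not stop anyone deducing the end of a block.
- **EP test after consent.** Whoever approaches a caregiver does not yet know whether the child will be randomized at all. This weakens steering at the approach without removing it.
- **Use of list numbers.** The Day 0 Procedure gives every enrolled child a study ID, while only iron-deficient children are randomized. If the others use up list numbers, some allocations may go unseen and predictability would be somewhat lower. The text does not settle this.
- **Separate roles.** The document does not say that the medical officer who approaches families also opens envelopes or sees the running record.
- **Outcomes.** Isotope incorporation is measured in a laboratory, and the Aim 2 outcome is a change from Day 0. The issue is selection at entry, not biased measurement.

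Three stronger readings are tempting and are not supported. A reader might infer that a third of allocations are known in advance. They are deducible, as an expected value, by someone who knows the block size and keeps count. A reader might also infer that two known allocations settle a block. They do so only when both went to the same arm, which happens in 1/3 of blocks; otherwise the third is still 50:50. Lastly, a reader might infer that enrolment will be selective or the results biased. Nothing in the protocol shows either, and the 33% and 70.8% measure predictability, not bias.

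**Conclusion.** The point holds as an avoidable weakness in concealment, not as an error or contradiction. With a constant, published block size of four on one sequence, an expected 33% of allocations can be deduced with certainty and a best guess is right 70.8% of the time. Both figures assume staff who know the block size, see earlier allocations and follow block boundaries, and that every list number leads to a visible allocation. Selective enrolment is possible but not shown; the existing safeguards reduce the opportunity for it without closing it. The change is worth making because it is cheap, at low priority.

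**What to change.** In the Randomization paragraph:

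1. Replace the constant block size by randomly varying sizes, for example 4 and 6, or 4, 6 and 8. Record the sizes only in a restricted document held with the list at the University of Minnesota, and remove them from the protocol and all site documents. Withholding the sizes matters because varying them alone hardly lowers the guessing rate for staff who know the possibilities.
2. State that the next envelope is opened only after consent and a qualifying EP result are recorded and the child's ID is written on the envelope. The EP test already comes before randomization in the Day 0 Procedure, so this tightens the looser wording about opening at enrolment.
3. Say whether children who are not iron-deficient use up numbers from the list of 100.

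The off-site generation of IDs and the sealed, ID-linked envelopes are already in place and stay as they are.

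The cost is regenerating one list of 100, or the unused envelopes if enrolment has begun, and a possible final difference of up to 3 or 4 children between arms, with negligible loss of precision. No clinical procedure changes.
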